### Randomization

Assignment of schools to the control or intervention condition is carried out according to the International Council for Harmonisation guidelines [32] and performed by a researcher not involved in the day-to-day conduct of the trial. Schools are allocated to a single condition (cluster design) to avoid contamination and for administrative convenience [33]. A minimization approach [34,35] is used to ensure balance across conditions in terms of the Index of Community Socio-Educational Advantage level (<1000 vs ≥1000), gender mix (coeducational vs single sex), and year level involved (year 9 students only vs multiple or other years). Minimization is undertaken in StataCorp LLC Stata statistical software version 14.2 using the rct_minim procedure [36]. The pool of already available schools is sorted in random order using the Excel 2003 data analysis random number generator and entered into the minimization routine in ascending order using the factors specified above. Subsequent schools are assigned to an intervention arm using rct_minim in the order that they join the trial and provide complete information. As this trial uses a no-treatment comparator control group, participants and researchers are not blinded to the allocation assignment.

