### Participants

#### Inclusion Criteria

All secondary students from the participating year groups, aged between 11 and 19 years, who attend one of the participating schools, are invited to participate. Both males and females are eligible. Participants are required to have an active email address for the duration of the trial. Only those students who can read and understand English and provide their signed written consent are able to participate in the research study and use the service. All participants can access their own mental health support or treatment throughout the trial.

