### Recruitment

The flow chart used to outline recruitment, randomization, and participation for this trial is provided in Figure 2.

To recruit schools, the study advertisement is circulated by email to NSW school counsellors who subscribe to the Black Dog Institute’s mailing list. Counsellors are invited to express an interest in the study by contacting the chief investigator (CI) by email. The CI responds to these emails with a study information pack and schedules a phone call to explain the study process and answer additional questions. Schools are informed that the study is available to students in any year group but is considered by the research team to be well suited to students in Grade 9 (ages 14 to 15 years), as half of all lifetime mental disorders emerge during the mid-teens [1]. To recruit students, a set of Student Information Forms are mailed to each school and distributed to students by a school staff member before the baseline assessment. Interested students are asked to review the material, discuss with their parents/guardians, and consider study participation.

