#### Demographics

At baseline, students provide their name, email, mobile phone number (optional), gender, and date of birth. Students are asked to report their current employment status (answered part-time, casual, or nil) and whether they identify as Aboriginal and or Torres Strait Islander (answered yes, no, I’d rather not say) or Lesbian, Gay, Bisexual, Trans or Intersex (answered yes, no, I’d rather not say).

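### The two-level gender-mix factor in the minimisation cannot balance boys' against girls' schools, and makes a complete split between arms more likely if both kinds enrol in similar numbers

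*Protocol article*

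**What the plan says.** The protocol article's Randomization section allocates whole schools by minimisation: "Minimization is undertaken in StataCorp LLC Stata statistical software version 14.2 using the rct_minim procedure". There are three factors, each with two levels:

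- the first: "Index of Community Socio-Educational Advantage level (<1000 vs ≥1000"
- the second and third, in one phrase: "gender mix (coeducational vs single sex), and year level involved (year 9 students only vs multiple or other years"

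The stated purpose is balance between conditions on these factors. No favoured-arm probability is given.

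Eligibility is broad. Inclusion Criteria admits both sexes, "aged between 11 and 19 years", and Recruitment adds: "Schools are informed that the study is available to students in any year group". Student "gender, and date of birth" are recorded at baseline (Demographics).

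The Results section reports 22 schools randomised, 10 to intervention and 12 to control. It does not say how many were single-sex, or of which sex. The Analysis section names school as a random effect and works from change or baseline-adjusted scores. It names no gender or age term.

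**The concern.** Minimisation steers each new school towards the arm that holds fewer schools of its type. Here the type is single-sex, whichever sex that is. Once a boys' school is in one arm, a girls' school that joins later is pushed to the other arm, and the routine scores the result as balanced. With so few schools, a handful of single-sex ones largely fixes the gender mix of each arm.

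Gender may plausibly relate to help-seeking intentions, depression and anxiety, and to change in them. Adjusting for the factor as coded would not help, because the code does not separate boys' from girls' schools. A school random effect allows for clustering but does not remove a between-arm difference in composition.

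**Working it through.** The protocol states no balance figure, so there is nothing of its own to reproduce.

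**Inputs from the protocol.** 22 schools; three two-level factors.

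**Assumptions, not in the protocol.** The numbers of boys' (b) and girls' (g) schools; a favoured-arm probability of 1.0 or 0.8; the other two factors at 50:50; schools arriving in random order.

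**Measure.** D = sum over single-sex schools of sex (+1 boys', −1 girls') × arm (+1 or −1). D = 0 means no gender imbalance from these schools. Let n = b + g.

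**Theory.**
- Simple randomisation: Var(D) = n.
- Single-sex schools split exactly evenly (n even): Var(D) = n + [n − (b − g)²]/(n − 1).
- So pooling raises the variance only when (b − g)² < n. Example 2+2: 4 + 4/3 = 5.33 against 4. Example 0+4: 4 + (4 − 16)/3 = 0 against 4.

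**Simulated RMS of D** (60,000 minimisations per cell, 22 schools, marginal balance; simple randomisation is √n):

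| Boys' + girls' | (b − g)² vs n | Simple | Pooled, 1.0 | Pooled, 0.8 | Three-level, 1.0 |
|---|---|---|---|---|---|
| 1+1 | 0 < 2 | 1.41 | 1.86 | 1.67 | 1.60 |
| 2+1 | 1 < 3 | 1.73 | 1.91 | 1.85 | 1.42 |
| 2+2 | 0 < 4 | 2.00 | 2.26 | 2.18 | 1.28 |
| 3+3 | 0 < 6 | 2.45 | 2.67 | 2.61 | 1.78 |
| 4+2 | 4 < 6 | 2.45 | 2.52 | 2.50 | 1.34 |
| 3+1 | 4 = 4 | 2.00 | 2.00 | 2.00 | 1.68 |
| 4+1 | 9 > 5 | 2.24 | 2.06 | 2.09 | 1.49 |
| 0+2 | 4 > 2 | 1.41 | 0.73 | 1.11 | 0.73 |
| 0+4 | 16 > 4 | 2.00 | 0.75 | 1.31 | 0.76 |

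With only one kind enrolled, the pooled and three-level rules are the same rule, so the last two rows differ only by simulation error.

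**Chance of a complete opposite split.**
- 1+1: about 86–87% pooled with no random element and about 67–70% at 0.8 (the spread reflects how imbalance is scored and simulation error). Simple randomisation gives 50%; a fixed 11:11 allocation gives 11/21 = 52%. The three-level rule gives 64%.
- 2+2: about 29% pooled and 20–21% at 0.8. Simple randomisation gives 2/16 = 12.5%; a fixed 11:11 allocation gives 13.8%. The three-level rule gives about 5%.
- 3+3: about 8–9% pooled and 6% at 0.8. Simple randomisation gives 2/64 = 3.1%.

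**Excess in RMS, pooled (1.0) over simple.** 1+1: 1.86/1.41 = 1.31. 2+1: 1.91/1.73 = 1.10. 2+2: 2.26/2.00 = 1.13. 3+3: 2.67/2.45 = 1.09. 4+2: 2.52/2.45 = 1.03. Smaller runs of 6,000 put the 2+1, 2+2 and 3+3 excess at 10–14%.

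**On the outcome scale.** With 11 equal schools per arm and half the students female in coeducational schools, the between-arm difference in percentage female is 100 × |D|/22 points. For 2+2 the RMS is 2.26/22 = 10.3 points pooled against 2.00/22 = 9.1 simple, an excess of 1.2 points. If gender shifts the analysed outcome by 0.1–0.5 SD (assumed), the excess is 0.0012–0.006 SD, or 0.6–3% of the planned effect of 0.20.

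**The case against.** The strongest reply is that the direction depends on a mix the protocol does not report, and nothing shows that both boys' and girls' schools enrolled. That stands. A reader might infer that the rule makes gender imbalance more likely than plain randomisation in general. It does not: at 3+1 the two are equal, at 4+1 pooling has the lower RMS, and with one kind only it roughly halves the RMS or better when there is no random element. Even at 2+2 the chance of any imbalance falls, from 62.5% to about 43%, while the complete split becomes more frequent.

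It is also tempting to quote the size of one opposed pair as the harm: 2/22 = 9.1 points, which at 0.1–0.5 SD is 0.009–0.045 SD, or 5–23% of 0.20. That compares with perfect balance rather than with randomisation. It also ignores the change-from-baseline and baseline-adjusted analyses, which remove much of any stable gender difference. Gender differences in change would remain.

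Nor does the text give false assurance about students: it aims for balance on school categories, not on student gender or age. The direction of any imbalance is random, so this is chance imbalance, not systematic bias.

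For year level, the pooling is there in the wording: a Year 7-only and a Year 12-only school would share a level. But the protocol does not show that such schools joined, and Recruitment steers schools towards Grade 9. No consequence has been demonstrated.

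Finally, covariate lists are often left to an analysis plan that is not shown. Their absence is therefore not the fault here. The point rests on the factor that the protocol does fix.

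**Conclusion.** The point holds in a conditional form. The gender-mix factor cannot tell boys' from girls' schools. When the two are similar in number, (b − g)² < n, it raises typical gender imbalance and makes a complete split more frequent than simple randomisation would. The effect is marked with one of each and modest otherwise, and it shrinks if the routine has a random element. When the numbers are clearly unequal, pooling is neutral or better in RMS.

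A three-level factor was at least as good as pooling in every mix tested. It is not a full cure: with one school of each kind its RMS (1.60) still exceeds that of simple randomisation (1.41). All these sizes rest on the assumed mix, favoured-arm probability and 50:50 split of the other factors. This is a cheap improvement to a stated rule, not an error that invalidates the trial.

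**What to change.** For any school still to be allocated, replace the factor by coeducational / boys only / girls only. The cost is slightly sparser minimisation cells.

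For the 22 schools already allocated, only the analysis can change. Add student gender and age (from date of birth) as fixed covariates in the primary mixed model, the analyses of covariance and both logistic models. Report the gender and age distribution by arm, with the number of boys', girls' and coeducational schools in each. The age term also covers the year-level remark.

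Specify the covariates before the arm comparison is seen. The article describes the data as under analysis, so if that point has passed, present the adjusted results as a labelled sensitivity analysis. The cost is two extra model terms, which is small against a target of 1600 students. In the logistic models the odds ratio becomes conditional on gender and age as well as on the baseline response.

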### Ethics Approval

Ethics approvals are obtained from the University of New South Wales (UNSW) Human Research Ethics Committee (HREC; HC17910), the State Education Research Applications Process (SERAP) for the NSW Department of Education (SERAP 2016471), the Sydney Catholic Schools (SCS) Research Centre (20186), and the Catholic Schools Office Diocese of Maitland-Newcastle.

### Setting

This trial is conducted in government, independent, and Catholic secondary schools located throughout NSW, Australia.

### Participants

#### Inclusion Criteria

All secondary students from the participating year groups, aged between 11 and 19 years, who attend one of the participating schools, are invited to participate. Both males and females are eligible. Participants are required to have an active email address for the duration of the trial. Only those students who can read and understand English and provide their signed written consent are able to participate in the research study and use the service. All participants can access their own mental health support or treatment throughout the trial.

#### Exclusion Criteria

Schools are required to have a school counsellor available onsite for the school visits and for the duration of the study.

**Table 1 table1:** Standard Protocol Items: Recommendations for Interventional Trials Compliance: Items from the World Health Organization dataset.

Data category	Information
Primary registry and trial identifying number	Australian New Zealand Clinical Trials Registry (ANZCTR): ACTRN12618001539224
Date of registration in primary registry	September 14, 2018
Secondary identifying numbers	—^a^
Source(s) of monetary or material support	Hong Kong and Shanghai Banking Corporation
Primary sponsor	Black Dog Institute, University of New South Wales
Secondary sponsor(s)	—
Contact for public queries	[name] [name] [contact]
Contact for scientific queries	[name] [name] [contact]
Public title	Smooth Sailing: Evaluating an online service for student well-being
Scientific title	Smooth Sailing: Evaluating an online service for student well-being
Countries of recruitment	Australia
Health condition(s) or problem(s) studied	Depression, anxiety, help-seeking for mental health
Intervention(s)	Intervention: A Web-based school-based mental health service for secondary students (Smooth Sailing); based on the principles of stepped care; 12-week duration
Control	Control: school-as-usual; waitlist
Key inclusion and exclusion criteria	Inclusion: Male and female secondary students; currently attending high school at 1 of the participating schools; have an active email address for the duration of the trial; Exclusion criteria: nil
Study type	Study type: Interventional; Allocation: Randomized; Intervention model: Parallel assignment; Primary purpose: Prevention
Date of first enrolment	February 22, 2018
Target sample size	1600
Recruitment status	Completed
Primary outcome(s)	Help-seeking intentions (measured using the General Help-Seeking Questionnaire). Primary timepoint: 12-week endpoint
Key secondary outcomes	Help-seeking behavior (measured using the Actual Help-Seeking Questionnaire); Symptom levels of: Distress (measured using the Distress Questionnaire-5); Depression (Center for Epidemiologic Studies Depression Scale-Child Version); Anxiety (measured using the Generalized Anxiety Disorder Questionnaire 7-item); Mental health literacy and stigma (measured using the Mental Health Literacy and Stigma Scale); Barriers to seeking help (measured by the Barriers to Seeking Help-Brief Scale); Functioning (measured by 1-tem scale). Primary timepoint: 12-week endpoint
Ethics review	Approved by University of New South Wales Human Research Ethics Committee on November 24, 2017
Completion date	June 29, 2018
Summary results	Data currently under analysis
Individual participant data sharing statement	Plan to share individual participant data (No)

^a^Not applicable.

### Recruitment

The flow chart used to outline recruitment, randomization, and participation for this trial is provided in Figure 2.

To recruit schools, the study advertisement is circulated by email to NSW school counsellors who subscribe to the Black Dog Institute’s mailing list. Counsellors are invited to express an interest in the study by contacting the chief investigator (CI) by email. The CI responds to these emails with a study information pack and schedules a phone call to explain the study process and answer additional questions. Schools are informed that the study is available to students in any year group but is considered by the research team to be well suited to students in Grade 9 (ages 14 to 15 years), as half of all lifetime mental disorders emerge during the mid-teens [1]. To recruit students, a set of Student Information Forms are mailed to each school and distributed to students by a school staff member before the baseline assessment. Interested students are asked to review the material, discuss with their parents/guardians, and consider study participation.

**Figure 2 figure2:**
[figure not shown]
Consolidated Standards of Reporting Trials flow diagram that will be used to illustrate participation throughout the phases of the Smooth Sailing Cluster Randomized Controlled Trial.

### Consent

For school consent, schools are asked to provide a signed letter of support from the school principal. This letter is then forwarded to the governing ethics bodies to confirm school participation. Individual student consent is provided by a signed copy of the Participant Information and Consent Form (PICF) that is obtained on the day of the baseline assessment. For all schools other than those in the Sydney Catholic Diocese, an opt-out consent process is employed for parental consent. In these schools, parents are notified of the study using the school’s usual methods of communication (eg, school newsletter). Parents are given 14 days to inform the school if they do not wish for their child to participate and can withdraw their child at any time. Students from schools in the Sydney Catholic Diocese are required to obtain signed parental consent. The PICFs for SCS are distributed to students 2 weeks before the baseline assessment. On the day of the baseline visit, PICFs are checked by the researchers to ensure student and parent consent is provided.

### Withdrawal of Consent

The PICF informs participants that taking part is completely voluntary and that they are free to withdraw from the study at any time without penalty and without having to give a reason. Participants can withdraw by emailing the research team or notifying the researchers at the school visits. Parents can also withdraw their child at any time using the same methods or by contacting their child’s school.

### The Intervention

The Smooth Sailing service is accessed using a website that requires students to register using a unique code. At registration, students complete an additional consent measure (a 6-item Gillick Competency Test) to ensure they understand the terms and conditions of the service. After correctly completing this measure, students are asked to input their code, provide their email address, mobile phone number (optional) and create a password. Once registered, the students complete a step assessment. This consists of reliable and valid measures of depression and anxiety symptoms [21]. The 9-item Patient Health Questionnaire-9 (PHQ-9) [21] is used to measure the presence of depressive symptoms over the past 2 weeks, with items rated on a scale from not at all (0) to nearly every day (4). The service also uses the Generalized Anxiety Disorder Scale-7 (GAD-7) [22] to measure the presence of anxiety symptoms in the past 2 weeks using the same response options as the PHQ-9. Students’ total scores on the PHQ-9 and GAD-7 scales are used to allocate them to a step of care (see Table 2).

After the step assessment, the Smooth Sailing service produces a personalized dashboard that provides students with an overview of their recommended activity. The Web-based psychoeducation consists of 5 10-min modules that provide information about anxiety, depression, and help-seeking (see Table 3). The modules were created specifically for the Smooth Sailing service and were reviewed in the co-design process by young people as well as a clinical psychologist. The content was also edited by a copywriter to ensure it was written at an appropriate reading level. The modules are complemented by animations and illustrations as well as hyperlinks to other credible youth mental health services and websites. All modules are self-paced and can be completed in any order. Module 6 includes referral to 2 Web-based, publicly available, free evidence-based CBT programs for depression and anxiety [37-39]. MoodGym [40] comprises 5 modules in which young people learn a range of strategies to identify and manage unhelpful patterns of thinking, connect their thoughts to their feelings, reduce worry, and improve self-esteem and interpersonal relationships. The BRAVE Program [41] includes 10 1-hour self-directed sessions that are usually completed over 10 weeks that teach young people to identify anxiety and stress, develop relaxation and problem-solving skills, and reframe negative thinking. These programs are provided to any student who is allocated to Steps 2, 3, and 4 throughout the study period.

**Table 2 table2:** Smooth Sailing service model: step criteria and intervention provided.

Criteria		Step				
		0	1	2	3	4
Score range		0-4	5-9	10-14	15-19	20+
Symptom severity		Nil	Mild	Moderate	Moderately severe	Severe
**Interventions provided**						
	Web-based psychoeducation	Yes	Yes	Yes	Yes	Yes
	Self-directed Web-based cognitive behavioral therapy	No	No	Yes	Yes	Yes
	Face-to-face sessions with a school counsellor to provide counselling and/or referral to external services	No	No	No	Yes	Yes

**Table 3 table3:** Module overviews.

Title	Content description
What is mental health?	Information about mental health issues that are common among youth and when it might be time to seek help
Feeling on edge	Information on anxiety, how to identify it, potential causes, where to seek help, and practical tips for managing it
Waves of sadness	Information on depression, differences between sadness and depression, potential causes, how and where to seek help, and practical tips to cope
When it’s time to tell someone	Information about when to seek help, how to talk to friends and parents, seek help from a general practitioner, and the roles of different health professionals
When a mate needs a hand	Ways to help others including having a private chat, seeking help together, respecting the treatment process, and the importance of looking after yourself
Don’t fret, help is here	Offers access to 2 evidence-based, free Web-based cognitive behavioral therapy programs, produced by Australian universities. Young people can select which program they prefer

In the Smooth Sailing service, school counsellor follow-up notifications are initiated if a student is allocated to Steps 3 or 4 or if a student reports having thoughts that they would be better off dead or thoughts of hurting themselves in the past 2 weeks (ie, score >0 on item 9 of the PHQ-9). School counsellors conduct the follow-up sessions during school time but after completion of the researcher visit. School counsellors follow their normal school protocols and duty of care procedures when attending to the notified students, initiating external referrals and parental contact when necessary.

For the duration of the study period, the Smooth Sailing service sends a fortnightly check-in survey to participants via email or SMS text messaging. This consists of the PHQ-2 and GAD-2 and is designed to test participants’ engagement and adherence to monitoring. These are ultrabrief versions of the longer counterparts and measure the presence of depression and anxiety symptoms in the past 2 weeks, with responses scored the same as the full scale [42]. Total scores range from 0 to 12. Users are reminded to use the Smooth Sailing program through email and SMS text messaging notifications that are sent fortnightly, on alternate weeks to the check-in survey. Every 6 weeks, a step assessment is completed which reallocates the level of care, depending on participants’ results. In accordance with the Australian Clinical Practice Guidelines for the Treatment of Depression in Adolescents and Young Adults [23], if a participant has not responded (ie, symptoms remain elevated or have worsened) within 6 weeks, they are stepped up to the next level of care. The combined step allocation accounts for the participants’ previous step, their current step, and whether there has been any change (See Table 4 for stepping decisions). Given that the service is in its infancy and its effectiveness is yet to be established, there is no stepping down in the current model. As such, no care is removed from participants, and they are instructed to continue using the service as advised by their updated personalized dashboard. Participants who show improvements can continue to use the Web-based CBT programs and all other modules as they wish.

The data collected by the service are stored securely on the Black Dog Institute research platform, which is supported by the UNSW servers. The school counsellor receives real-time notifications for students who require follow-up via a secure, purpose-built Web-based portal. The school counsellor can log into the portal to identify the students requiring follow-up and utilize their usual duty of care and referral pathways to treat students. Using the portal functions, school counsellors can notify the research team that follow-ups have been completed. There is also the option for counsellors to provide case notes, detailing treatment action and any adverse events. School counsellors are also able to view these participants’ use of the Smooth Sailing program, including module completion. School counsellors receive an automated email reminder to check the portal after every assessment point. Researchers also receive email notifications for any student who triggers a notification. No identifiable information is contained in these emails.

